### **1.3. Trial design**

The EfRAMAS project is a randomized, controlled, non-inferiority clinical trial. Randomization will be done at the individual level in each of the 14 UNTAs selected for the study.

Bulk randomization of variable size will be used. After randomization, the participants will be distributed randomly either in the control group or in the intervention group.

Each participant will receive the dose of RUTF corresponding to the group to which he belongs: standard dose for the control group and reduced dose for the intervention group (Table 2).

Apart from nutritional support, participants will also receive systematic medical treatment (Table 5).

After recovery (according to the admission criteria, if  $PT \geq -1.5$  z-score at two consecutive weighings, and  $PB \geq 125$  mm and absence of nutritional edema for 14 days), follow-up of participants will be ensured every 15 days up to 3 months after discharge as provided for in the national protocol (12). During this follow-up, the children will receive medical treatment if necessary according to the symptoms (malaria, etc.) and a nutritional product (fortified flour or ASPE) if available. Children who develop complications during treatment will be referred to UNTI and then return to their respective study group after the complication has been resolved.

[figure not shown]

Figure 1 : Design selection, randomization and monitoring of participants

## **II. Methodology**

### **2.1. Participants, interventions and outcomes**

#### **2.1.1. Study framework**

The EfRAMAS project will be carried out in 14 UNTAs in the health zones of Bonzola and Nzaba, in the province of Kasai Oriental in the DRC.

Kasai Oriental is part of the provinces of the greater Kasai area, which is made up of 5 provinces. In 2017, the area of Greater Kasai was the victim of a conflict between the militiamen of Kamwina Nsapu and the Armed Forces of the DRC. Starting from the province of Kasai Central, the conflict spread to affect all the provinces of the Grand Kasai area. It is one of the bloodiest conflicts in the Greater Kasai area, with more than 5,000 dead, 1.4 million displaced people and more than 600 schools and health centers destroyed.(27) (28) (29). In addition to schools and health centers, the militiamen loot and ransack everything they cannot take.

More than 70% dependent on agriculture, the population of Kasai loses not only crops (for seasons A, September - December 2016 and season B, February - July 2017) but also tillage equipment. This resulted in an inflation of more than 100% with as a corollary the worsening of malnutrition of children under 5 and pregnant women.(30) (31). According to forecasts from the integrated analysis of food and nutritional security (IPC) carried out in September 2020, more than 31% of the population of Kasai Oriental will be in a situation of very high food insecurity by June 2021.(32).

These two ZS are located in the city of Mbuji Mayi, capital of the province of Kasai Oriental (Figure 1). The Bonzola ZS has 15 health centers (CS) and 1 General Reference Hospital and the Nzaba ZS has 18 health centers (CS) and 1 General Reference Hospital. Each ZS has an UNTA. The average admission per month was 401 and 635 MAS children respectively in the ZS of Bonzola and Nzaba, at the start of 2021. With the exception of the 2 UNTAs in Bonzola and 5 in Nzaba, all these UNTAs are functional and organize screening. active. Regarding staff training, a total of 32 (14 women and 18 men) and 27 (16 women and 11 men) providers respectively in Bonzola and Nzaba are trained on PCIMA. For the Integrated Management of Childhood Illnesses (IMCI), only 4 providers (1 woman and 3 men) are trained in the Bonzola health zones only. A man and a woman are trained on Reproductive Health in Bonzola against two men and a woman in Nzaba. Of the 1,241 Community Relays in the ZS de Bonzola, 1,004 of them or 81% are active, including 125 trained in active screening, 110 in ANJE and 11 in

maternal PB. In Nzaba, only 662 of the 1290 RECOs are active, including 10 trained in active screening and 30 in IYCF.

The DRC has not been spared by the COVID pandemic. It has recorded a cumulative 36,576 confirmed cases and 1 probable case as of June 16, 2021 since the epidemic was declared on March 10, 2020, including 857 deaths, i.e. a case fatality of 2.3%. Fortunately, the province of Kasai Oriental is not one of the most affected provinces. It has recorded 24 confirmed cases since the start of the pandemic and has experienced a period of at least 29 days without recording cases (Situation report n 167/2021 of 16/06/2021 from the Ministry of Health).

In the third quarter of 2020, the ZS of Bonzola and Nzaba reported respectively i) 33% and 30% of children under 5 years of age malnourished with a MUAC <125 mm according to data from the sentinel sites and ii) 23% and 26 % of malnourished pregnant women with a MUAC <230mm, ie these two areas are reported on nutritional alert in the SNSAP bulletin of August 2020. The two health areas are priority n ° 2 of the revised humanitarian response plan (33).

In January and February 2021, the health situation in the ZS is summarized by the following table:

Chart 1 : Health situation, Nzaba and Bonzola health zones, January and February 2021

| Indicators                                       | ZS Bonzola     | ZS Nzaba       |
|--------------------------------------------------|----------------|----------------|
| Acute respiratory infection in children <5 years | 314 (1%)       | 895 (2%)       |
| Malaria (Attack rate) in children <5 years       | 2,629 (7%)     | 2,986 (5%)     |
| Diarrhea (Attack rate) in children <5 years      | 4,104 (10.20%) | 7,644 (11.64%) |
| Measles (Attack rate) children <5 years          | 4              | 8              |
| HIV in the general population                    | 3.99%          | 2.25%          |
| Women who adopted FP                             | 31.42%         | 12.51%         |
| Mothers / caregivers sensitized to IYCF          | 52.64%         | 81.12%         |
| Exclusive breastfeeding in children <6 months    | 70.69          | 93.4           |
| IMCI access for children <5 years old            | 96.59%         | 69.52%         |
| Anti-measles vaccines for children <5 years      | 1,164 (3%)     | 2,080 (4%)     |
| Vit A (dose) children <5 years                   | 9,150          | 16,750         |
| MAS in 2020 (SMART ACF month, 2020)              | 2,382 (7%)     | 2,106 (4%)     |

Source: Data from the ACF survey on Mbuji Mayi (2020)

The populations of these 2 ZS live mainly from agriculture and artisanal diamond mining (95%). Geographical accessibility (road and air) is relatively good and there is good telephone coverage. The province experiences two periods of welds (February - March and September - November). The population has poor access to drinking water.

At the same time as the EfRAMAS project will take place, ACF will lead a support intervention to the Ministry of Health for the management of acute malnutrition in these 2 HZs.

The main axes of this technical support are:

- Integrated Management of Severe Acute Malnutrition (PCIMA);
- Integrated Management of Childhood Illnesses (IMCI);
- Family planning ;
- Prenatal Consultations (ANC);
- Post-Natal Consultations (CPON).

In order to materialize its support, ACF organizes the following activities:

- Capacity building of health care providers;
- Bonuses for the functioning of health facilities and the encouragement of service providers;
- Strengthening of the community component by giving bonuses to community relays;
- Support for trained providers;
- Provision of care monitoring tools;
- Supply of inputs including RUTF, drugs etc.

[figure not shown]

Figure 2 : Study site map, ZS Bonzola and Nzaba, Kasai Oriental, DRC

Apart from ACF, other partners have supported or are supporting the ZS of Bonzola and Nzaba.

### 2.1.2. Participants

#### a. Inclusion criteria

To participate in this study, individuals must meet the following criteria:

- Be between 6 and 59 months old;

- To be MAS: PT <-3 Z-score and / or PB <115mm and / or bilateral edema (+, ++);
- Not having any medical complications;
- Have a good result on the appetite test;
- Live in the selected health zone;
- Consent to participate in the study (informed consent);
- Not have other siblings already admitted to the study. When there are several participants in the same siblings, only the first will be included in the EfRAMAS project. The others will be covered according to the national program but will not be part of the study.

### Non-inclusion criteria

- Appetite test inconclusive (negative test)
- Have another sibling member (MAS) already admitted to the study;
- Have a declared allergy to peanuts and / or milk;
- Have received treatment for SAM in the past 6 months, including readmissions after program drop-out, relapses and medical transfers;
- Malformation or disability or chronic pathologies that may affect food intake, such as a cleft palate, cerebral palsy, trisomy 2, sickle cell anemia ...

### 2.1.3.Intervention

As part of the EfRAMAS project, the intervention will consist of the management of SAM with all the care provided for in the national protocol. The only difference will be in the dosage of RUTF over time. Both groups will receive the same dose of RUTF for the first two weeks. Then in the intervention group, the reduction in the dose of RUTF will take place from the third week of treatment (Table 2). The intervention will begin concomitantly in both groups.

Chart 2 : Dose of RUTF per group in number of sachets per week

| Weight (kg) | Standard dose control group |               | Reduced dose intervention group |               |                    |               |
|-------------|-----------------------------|---------------|---------------------------------|---------------|--------------------|---------------|
|             | Admission-Discharge         |               | Weeks 1-2                       |               | Week 3 - discharge |               |
|             | Bags / week                 | Kcal / kg / d | Bags / week                     | Kcal / kg / d | Bags / week        | Kcal / kg / d |
| 3.0-3.4     | 9                           | 168-190       | 9                               | 168-190       | 7                  | 147-167       |
| 3.5 - 4.9   | 11                          | 183-204       | 11                              | 183-204       | 7                  | 102-143       |
| 5.0 - 6.9   | 14                          | 155-214       | 14                              | 155-214       | 7                  | 72-100        |
| 7.0 - 9.9   | 21                          | 144-204       | 21                              | 144-204       | 14                 | 101-143       |
| 10.0 - 14.9 | 28                          | 144-214       | 28                              | 144-214       | 14                 | 67-100        |

When a participant does not respect his date of appointment, the day he presents for the consultation, he will receive the number of sachets in proportion to the number of days remaining before the next appointment.

### **a. Criteria for transfer to UNTI**

In accordance with the criteria set in the PCIMA protocol, the intervention will be interrupted and the child transferred to the UNTI if he finds himself in one of the following cases:(12) :

#### ***On admission:***

- Any child under 6 months with a weight <3.5 kg;
- Mixed forms of malnutrition (marasmus and kwashiorkor);
- Presence of generalized edema (+++);
- If the appetite test fails (poor appetite);
- Presence of signs of medical complications.

#### ***During the weekly consultation:***

- Increase / development of nutritional edema;
- If the appetite test fails (poor appetite);
- Appearance of signs of medical complications;
- Appearance of re-nutrition diarrhea leading to weight loss;
- Presence of one of the "treatment failure" criteria:
  - Weight loss for 2 consecutive weeks;
  - Weight loss of more than 5% of body weight at any one visit;
  - Weight stagnant for 3 consecutive weighings.

All the children admitted to the study and who will be transferred to UNTI, will then return to research in their respective groups. On their return, the children in the reduced dose arm will resume the planned dose the week they were transferred, so they do not restart the treatment from zero but continue it.

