##### **Secondary objectives**

To assess the effectiveness of a reduced dose of RUTF in the management of SAM in terms of:

- **Duration of edema melting** (in days) since admission.
- **Duration of stay** (in days);
- **Performance indicators (cure rate, dropout, mortality, non-respondent, transfer to hospital)**
- **Treatment cost savings** (average cost and total cost per child treated);
- The growth velocity of anthropometric indices
- **Psychomotor development** children
- **Degree of acceptance** a reduced dose of RUTF by healthcare workers and the community
- **Relapse rate** up to 3 months after the “cured” exit from the program.

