### **b. Modification or interruption of the intervention**

During the implementation of this study, the intervention will be interrupted for each participant who presents (12):

- Withdrawal of informed consent;
- Discontinuation of treatment;
- Lost view ;
- Failure to process.

Chart 3 : Criteria for leaving the study outside of the cure

| Criteria                                        | Definition                                                                                                                                                       |
|-------------------------------------------------|------------------------------------------------------------------------------------------------------------------------------------------------------------------|
| Abandonment-confirmed                           | Patient absent for two consecutive weeks (declared abandonment in the third) sought by the RECOs and confirmed as having abandoned                               |
| Unconfirmed abandonment                         | Patient absent for two consecutive weeks (declared abandonment in the third) but his actual method of discharge (abandonment or death) not having been confirmed |
| Death                                           | Participant whose death has been certified by a nursing staff                                                                                                    |
| Lost view                                       | Change of address, followed in another CS outside the study area                                                                                                 |
| Treatment failure                               | Referred to UNTI following the appearance of danger signs (temporary discharge *)                                                                                |
| Withdrawal of consent                           | Any time after randomization                                                                                                                                     |
| Non-response to treatment (even if very rarely) | Children who do not recover after 12 weeks of treatment                                                                                                          |

*\*AT their return the children of the arm with reduced dose will resume with the dose planned for the week in which they were transferred, so they do not restart the treatment from zero but continue it.*

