| Evaluate the duration of treatment for each participant in the two groups                    | Duration of the treatment                    | Time between admission and discharge (PB≥12.5cm or PT ≥-3 Z score or edema melt)                                                                                                         | number of days           | interval |
| Assess dropout, cure, treatment failure and mortality rates                                  | Dropout rate in each arm                     | Number of children who have abandoned treatment and who no longer come to the center even after 3 home visits / total of children followed in each arm                                   | percentage               | interval |
|                                                                                              | Recovery rate                                | Percentage of children having reached the discharge after 3 months of treatment                                                                                                          | percentage               | interval |
|                                                                                              | Proportion Transfer to hospital in each arm  | Number of children being transferred to hospital during treatment (3 months) following a medical complication or if stagnation or loss of appetite / total children followed in each arm | percentage               | interval |
|                                                                                              | Proportion of Deaths in each arm             | Number of children who died during the stay at UNTA or during transfer to UNTI / total child followed in each arm                                                                        | percentage               | interval |
| Evaluate the cost and savings made with a reduced dose of RUTF compared to the standard dose | % savings in SAM treatment with reduced dose | Difference in cost between treatment with standard dose and treatment with reduced dose, expressed in%                                                                                   | percentage               | interval |

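### The transfer-to-hospital outcome in Annex 8 does not name weight loss, although weight loss is a mandatory reason for transfer to the UNTI, and Chart 3 defines treatment failure in different terms

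*Protocol*

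**What the plan says.** Three places in the protocol bear on the same event.

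- **Section 2.1.3 a, weekly consultation.** The child is transferred to the UNTI if any listed case is met. The list is introduced with the words "In accordance with the criteria set in the PCIMA protocol". Three of its entries are grouped as treatment failure: "Weight loss for 2 consecutive weeks", "Weight loss of more than 5% of body weight at any one visit", and weight that stays flat over three weighings.
- **Section 2.1.3 b, Chart 3.** Treatment failure is defined as "Referred to UNTI following the appearance of danger signs (temporary discharge". No weight criterion appears.
- **Annex 8.** Under the objective "Assess dropout, cure, treatment failure and mortality rates", the transfer variable counts children sent to hospital during treatment "following a medical complication or if stagnation or loss of appetite".

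Transfer is an outcome as well as a care rule. The secondary objectives in section 1.2 list the performance indicators as "cure rate, dropout, mortality, non-respondent, transfer to hospital".

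**The concern.** The rule that creates transfers and the variable that counts them do not name the same causes. The cause left out is one the trial has reason to watch. From week 3, Chart 2 cuts the weekly ration in the intervention arm by between 22% (9 to 7 sachets) and 50% (14 to 7, or 28 to 14). If the smaller ration harms some children, weight loss is a plausible first sign, and section 2.1.3 a would then send them to the UNTI.

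An analyst who applies the Annex 8 wording strictly would leave those transfers out. An excess in the reduced-dose arm could then be missed by the indicator meant to show it. Someone working from Chart 3 would have to decide what counts as a danger sign, and the 14 sites might decide differently. The protocol has fixed the definitions itself and they disagree, so this is not a detail left for an analysis plan.

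**Working it through.** No figure in the plan enters this point. The sample size rests on weight-gain velocity, not on transfers. The check is a comparison of texts.

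**Step 1. Triggers against definitions.** Inputs: the weekly-consultation list in section 2.1.3 a, the transfer variable in Annex 8, and the treatment-failure row of Chart 3.

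| Trigger in section 2.1.3 a | Labelled treatment failure there? | Named in Annex 8? | Named in Chart 3? |
|---|---|---|---|
| Oedema appears or worsens | No | Only if read as a complication | Not named |
| Appetite test failed | No | Yes | Not named |
| Signs of medical complication | No | Yes | Not named; may be what danger signs means |
| Refeeding diarrhoea with weight loss | No | Only if read as a complication | Not named |
| Weight loss two weeks running | Yes | No | Not named |
| Loss above 5% at one visit | Yes | No | Not named |
| Flat weight over three weighings | Yes | Yes | Not named |

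Count: 4 general triggers + 3 treatment-failure triggers = 7. Annex 8 names 3 of the 7. Two more depend on a broad reading of complication, and 3 + 2 = 5. The remaining 7 − 5 = 2 are the weight-loss criteria.

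**Step 2. Can a broad reading bring weight loss in?** Not easily. Section 2.1.3 a lists complications and weight criteria as separate entries, so within this protocol they are different things. Annex 8 names one weight criterion, stagnation, alongside complication. That suggests its author did not treat weight criteria as already covered by complication.

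**Step 3. Size of the intervention.** From Chart 2, reduction in sachets per week from week 3: (9 − 7)/9 = 22%; (11 − 7)/11 = 36%; (14 − 7)/14 = 50%; (21 − 14)/21 = 33%; (28 − 14)/28 = 50%.

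**Step 4. Scale.** Annex 5 gives 500 children per arm, so each percentage point of transfers is 0.01 × 500 = 5 children. The documents state no expected transfer rate, overall or by cause. Purely as an assumption, an excess of 1 to 5 points in weight-loss transfers would be 5 to 25 children. This is a conversion, not a forecast.

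**Step 5. Reach.** The primary outcome is computed from weight at admission and discharge and treatment duration (Annex 8). A transferred child returns to the same arm. The definition of the transfer variable does not enter that calculation.

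**The case against.** The strongest reply is that the Annex 8 numerator is simply the number of children transferred to hospital during treatment, and that the causes after it are an abbreviated gloss. Section 1.2 names the indicator without restricting causes, and stagnation may be shorthand for all three weight criteria. An analyst would have to see a transfer made under the protocol and then discard it because a variable list was short. This is a fair reading, and on it every transfer counts. It stands as a limit on the point but does not remove it: nothing in the text says the list is illustrative, and Chart 3 adds a third wording.

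A second reply is that weight loss is watched elsewhere. It enters weight-gain velocity, may show in length of stay and cure, and is open to the monthly safety review in section 2.4.1. That is correct and lowers the stakes. It does not make the transfer indicator mean what it appears to mean.

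Three stronger readings are tempting, and the documents do not support them.

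- **A reader might infer that treatment failure has no variable in Annex 8.** The objective lists four items, and four variables follow: dropout, recovery, transfer and death. Since Chart 3 equates treatment failure with referral to the UNTI, transfer is plausibly its variable.
- **A reader might infer that the weight triggers misclassify children whose oedema is resolving**, since oedematous children are eligible ("To be MAS: PT <-3 Z-score and / or PB <115mm and / or bilateral edema"). The triggers are taken from a national protocol that is not at hand, and they apply equally in both arms. The documents give neither the share of oedematous children nor their fluid weight. Weight and oedema are recorded weekly (Chart 5), so such transfers can be identified afterwards.
- **A reader might infer an effect on the non-inferiority test.** None follows, for the reason in step 5.

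**Conclusion.** The point holds as a minor inconsistency between stated definitions. Transfer is mandatory for two weight-loss criteria that the Annex 8 transfer outcome does not name, and Chart 3 defines treatment failure by a term left undefined in the text shown. Followed literally, a secondary indicator omits a kind of failure that the reduced ration could plausibly increase.

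The size of the effect is unknown. It depends on how many transfers are triggered by weight loss in each arm, on which the documents are silent, and on whether the Annex 8 wording is applied strictly or as a description. The primary outcome and the sample size are unaffected, and no fault is found with the clinical triggers themselves.

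**What to change.** 1. **Annex 8.** Define the transfer variable as the number of children transferred to the UNTI during treatment for any weekly-consultation criterion in section 2.1.3 a. Keep the present denominator, and refer to that list in place of the three named causes.
2. **Chart 3.** Define treatment failure by reference to the same criteria in place of danger signs.
3. **Leave the triggers as they are.** No referral is delayed or added.

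A breakdown of transfers by resolving oedema is optional, since it can be derived from the weekly records.

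The cost is two reworded definitions, with no new measurement and no change in care. Under section 3.3 the change needs an entry in the amendment register and ethics committee validation. It is best made before outcomes are compared by arm, so that the choice of count cannot follow the results.
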